# Bee venom acupuncture, NSAIDs or combined treatment for chronic neck pain: study protocol for a randomized, assessor-blind trial

**DOI:** 10.1186/1745-6215-15-132

**Published:** 2014-04-21

**Keywords:** Chronic neck pain, Combined treatment, Bee venom acupuncture, NSAIDs

## Abstract

**Background:**

Chronic neck pain (CNP) is a common painful medical condition with a significant socioeconomic impact. In spite of widespread usage, the effectiveness and safety of combined treatments between conventional and complementary alternative medical treatment modalities has not been fully established in a rigorous randomized clinical trial (RCT). This pilot study will provide the clinical evidence to evaluate the feasibility and refine the protocol for a full-scale RCT on combined treatment of bee venom acupuncture (BVA) and non-steroidal anti-inflammatory drugs (NSAIDs) in patients with CNP.

**Methods/Design:**

This is a randomized, single-blind clinical trial with three parallel arms. Sixty patients between 18 and 65 years of age with non-specific, uncomplicated neck pain lasting for at least three months will be enrolled. Participants will be randomly allocated into the BVA, NSAIDs or combined treatment group. Assessors and statisticians will be blinded to the random allocation. All researchers will receive training to ensure their strict adherence to the study protocol. Patients from the BVA and combined treatment group will be treated with a bee venom increment protocol into predefined acupoints for six sessions over a three week period. BVA intervention is developed through a comprehensive discussion among interdisciplinary spine disorder experts, according to the guidelines of Standards for Reporting Interventions in Clinical Trials of Acupuncture (STRICTA). Patients from the NSAIDs and combined treatment groups will be prescribed loxoprofen (one tablet to be taken orally, three times a day for three weeks). Bothersomeness from CNP measured using a visual analogue scale (VAS) will be the primary outcome assessed at screening, visit two (baseline), four, six, eight (4th week assessment) and nine (8th week assessment) follow-up session. VAS for pain intensity, neck disability index (NDI), quality of life, depressive status and adverse experiences will also be analyzed.

**Discussion:**

Our study results will contribute to feasibility evaluation and to relevant RCT protocol development for a full-scale RCT on combined treatment of BVA and NSAIDs for CNP patients.

**Trial registration:**

This study is registered with the United States (US) National Institutes of Health Clinical Trials Registry: NCT01922466.

## Background

Non-specific chronic neck pain (CNP) is a common debilitating medical condition affecting 30 to 50% of the general population and is most prevalent in middle age [1]. In Korea, the cumulative lifetime prevalence of CNP is 20.8% [2]. CNP causes a significant socioeconomic impact related not only to direct medical costs, but also indirect health care costs and loss of productive capacity [1,3,4]. As a mechanical pain without an accurately identifiable pain source [5], CNP may be related to neck pain, upper extremity pain and headache, but is not related to apparent radiculopathies or myelopathies, including sensory and motor dysfunction [5,6].

Depending on the tailored treatment strategies, various treatment modalities are available for CNP including medication (non-steroidal anti-inflammatory drugs (NSAIDs), serotonin reuptake inhibitors and anti-epileptics), interdisciplinary rehabilitation, physical therapy, education, spinal injection and surgical interventions [7,8]. Although pain-relieving medication is most frequently used to alleviate CNP [9], longterm NSAIDs use is limited due to the risk of side effects and patient intolerance [7].

It is reported that neck pain patients tend to concurrently utilize both conventional treatment and complementary alternative medicine (CAM) in the hopes of more positive effects and safety profile [10]. The use of CAM therapeutic modalities including acupuncture, herbal medicine, herbal acupuncture, cupping and chiropractic manipulation has been increased [11-14]. Bee venom acupuncture (BVA) is one of the most frequently performed pharmacopuncture to alleviate neck pain [15,16]. As an acupoint-stimulating treatment, BVA is utilized for the treatment of neck pain, low back pain, acute ankle sprain, post-stroke shoulder pain, rheumatoid arthritis, lumbar disc herniation and osteoarthritis [16,17]. BVA has been reported to exhibit analgesic, anti-inflammatory, anti-arthritic and anti-cancer effects [18] in experimental animal models [19,20] and in clinical studies [15-17,21,22]. The analgesic effects of BVA are more potent with repetitive administration than with a single treatment [23].

Although combined treatments between conventional and CAM interventions have been frequently utilized, the effectiveness and safety has not been fully investigated in rigorously designed clinical trials. This study may be a preliminary evaluation of the non-inferiority of BVA against NSAIDs, and any synergistic or additional effect of each. The results from this pilot study will provide clinical evidence to evaluate the feasibility for full-scale randomized controlled trial (RCT) on combined treatment of BVA and NSAIDs for CNP.

## Methods/Design

### Trial design

This is a randomized, assessor-blind clinical trial with three parallel arms (1:1:1 ratio) conducted at the spine center at Kyung Hee University Hospital at Gangdong (KHUHGD). We will compare the effects of BVA, NSAIDs and the combined treatment of BVA and NSAIDs in patients with CNP. The trial has been registered with the United States (US) National Institutes of Health Clinical Trials registry (NCT01922466) and has been approved by the Institutional Review Board (IRB) of KHUHGD (KHNMC-OH-IRB 2012–019). Outcome assessment and statistical analyses will be performed by independent researchers who are blinded to the patient assignment (Figure 1).

**Figure 1 F1:**
[figure not shown]
Study flowchart.

### Participants

Sixty participants with non-specific neck pain will be recruited to the study from KHUHGD through advertisements in local newspapers, on hospital websites and on bulletin boards. All participants will be interviewed by telephone and scheduled for a screening visit by the clinical research coordinator (CRC). After completing the screening questions, participants will be guided through the informed consent process. Participants will be informed that they may be randomly allocated into any of the three treatment groups (BVA, NSAIDs and combined treatment), and that they may withdraw their voluntary participation at any stage. Patients will be provided enough time to deliberate their participation in the independent waiting room with the written information and the informed consent form. As a screening process for eligibility, a skin hypersensitivity test will be performed on each patient at LI11 acupoints, using a subcutaneous injection of 0.05 ml of a 1:20,000 bee venom preparation. Local swelling greater than 10 mm in diameter or redness greater than 20 mm in diameter will be considered a positive reaction, and these patients will be excluded from the study. Eligible participants will be randomly allocated into one of three parallel groups at a ratio of 1:1:1, (BVA:NSAIDs:combined treatment). After random allocation, the interviewer (CRC) will schedule treatment sessions. All recruitment procedures will be recorded in a log file.

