### Bee venom acupuncture

BVA will be prepared as dried bee venom powder (Yoomil Garden, Hwasun, Korea), diluted (1:20,000) and filtered in normal saline (0.9% NaCl) at the Korean medical pharmacy at KHUHGD. BVA treatment will be conducted using 26-gauge sterile disposable syringes (Green Cross Co., Yongin, Korea) containing bee venom diluted with normal saline (0.9% NaCl).

After sterile skin preparation, participants will be administered a perpendicular, subcutaneous injection at a depth of 0.5 to 1.0 cm with the patient lying in the prone position. The acupuncturist will treat participants under the predefined BVA protocol at predefined acupoints. BVA intervention will consist of six sessions twice a week for three weeks, under the following weekly BVA incremental protocol: 0.2 ml for the first week, 0.4 ml for the second week and 0.8 ml for the third week. The predefined points (SI12, SI14, BL11, BL12, TE15 and GB21) have been carefully selected from textbooks and research articles by a process of consensus among participating Korean medical doctors (KMD), all of whom are experienced in the treatment of chronic neck pain.

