### Outcomes

Assessment of neck pain-related dysfunction, pain and quality of life will be collected five times over eight weeks: at screening, visit two (baseline), four, six, eight (4th week assessment) and nine (8th week assessment) follow-up sessions. Medical history and sociodemographic characteristics, including age, gender, marital status, residence, occupation and education level will be taken from the screening visit. Any unpredicted, adverse events will be recorded at each visit (Table 1).

**Table 1 T1:** Schedule for data collection: outcome measures per visits

**Measures**	**Screening**	**Visit 2 (baseline)**	**Visit 4**	**Visit 6**	**Visit 8 (4th week assessment)**	**Visit 9 (8th week assessment)**
Sociodemographic characteristics	○					
Physical examination	○					○
Laboratory tests	○				○	
VAS for bothersomenesst of CNP	○	○	○	○	○	○
VAS for pain intensity of CNP	○	○	○	○	○	○
Neck disability index		○	○	○	○	○
EuroQol 5-Dimension		○	○	○	○	○
Beck’s depression inventory		○			○	○
SF-36		○			○	○
‘Skin roll’ test		○			○	○
Credibility test		○			○	
Adverse experiences*		○	○	○	○	○

*Adverse experiences will be monitored throughout the clinical trial.

CNP: chronic neck pain; VAS: visual analogue scale.

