### Primary outcome measurement

bothersomeness of chronic neck pain will be evaluated using the 10 cm visual analog scale (VAS) for CNP. Participants will be asked to report the degree of clinical severity and impact on activities of daily life experienced within the past week on a continuous discomfort scale of 0 to 10 (0, absence of discomfort; 10, the worst discomfort imaginable) [24] at screening, visit two (baseline), four, six, eight (4th week assessment) and nine (8th week assessment) follow-up sessions. The primary end point will be the VAS score at the four-week follow-up, one week after the completion of the three-week treatment session.

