#### The neck disability index (NDI)

Neck pain-related dysfunction will be assessed using the validated Korean version of NDI [26] at visit two (baseline), four, six, eight (4th week assessment) and nine (8th week assessment) follow-up sessions. The NDI contains 10 questions about pain intensity, personal care, lifting, reading, headaches, concentration, work, driving, sleeping and recreation. Each question is rated using a 6-point scale from 0 to 5 points (0, absence of problem; 5, disabled by neck pain).

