### Randomization and allocation concealment

A total of 60 participants will be randomly assigned following simple randomization procedures, with a 1:1:1 allocation ratio. The randomization sequence will be generated by an independent researcher using a computerized, random-number generator through a Microsoft Office Excel 2007 software package. Opaque envelopes labeled by study patient number will be conveyed to the interviewer (CRC). The CRC will open the sealed envelopes and allocate participants into the predefined treatment arms. Allocation concealment will not be broken until the completion of the study. The random allocation assignment will be performed only after a participant is confirmed to be eligible and written informed consent has been obtained. Detailed information, including the treatment arm and randomization number from an individual participant will be recorded in the case report form (CRF) and randomization table.

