### Planned statistical analysis

The analysis will be focused on exploring the feasibility and acceptability of protocol implementation and refining the protocol of future RCT. The results from hypothesis testing will be treated as preliminary and interpreted with caution. The results of this study may provide a preliminary evaluation of any synergistic or additional effect, and of the non-inferiority of combined treatment of BVA and NSAIDs. All statistical analyses will be carried out using the Statistical Package for the Social Sciences (SPSS) for Windows version 18.0 and will be expressed by mean and standard deviation. The level of significance will be set at *P* < 0.05. For each outcome variable, an analysis of covariance (ANCOVA) will be performed on the data to adjust baseline characteristics. Trends over time and time-by-treatment interactions will be explored using a repeated-measures analysis of variance (ANOVA). A Chi-square test or a Fisher’s exact test will be performed to determine differences between groups and adverse effects, which will be recorded and described as a frequency and percentage. Fisher's exact test is used when the cell whose expected value is less than 5 is equal or more than 20%.

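### The described order does not ensure that the visit 2 baseline is recorded before open-label patients learn their arm

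*Protocol article*

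**What the plan says.** Four parts of the protocol article bear on the order of events.

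- **Participants.** After telephone interview, screening, consent and the skin test, the text continues: "Eligible participants will be randomly allocated into one of three parallel groups at a ratio of 1:1:1, (BVA:NSAIDs:combined treatment". It then says: "After random allocation, the interviewer (CRC) will schedule treatment sessions".
- **Randomization and allocation concealment.** The condition for allocation is: "The random allocation assignment will be performed only after a participant is confirmed to be eligible and written informed consent has been obtained". Baseline measures are not part of it. The coordinator who books the sessions also opens the envelopes.
- **Outcomes and Table 1.** Visit 2 is labelled as the baseline. The two VAS scales are taken "at screening, visit two (baseline), four, six, eight (4th week assessment) and nine (8th week assessment) follow-up sessions". The NDI starts one visit later: "at visit two (baseline), four, six, eight (4th week assessment) and nine (8th week assessment) follow-up sessions". Table 1 likewise gives EQ-5D, BDI, SF-36 and the skin-roll test no screening value.
- **Planned statistical analysis.** For each outcome, "an analysis of covariance (ANCOVA) will be performed on the data to adjust baseline characteristics". The section does not say whether the screening or the visit 2 score is meant.

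The Blinding section lists the assessor, the prescriber, the pharmacists and the statistician as blinded. Patients are not listed, and the Interventions section describes no sham or placebo.

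**The concern.** A baseline covariate should be fixed before the patient can know the arm. If it is self-reported afterwards, hope or disappointment about the allocation can move it differently between arms. ANCOVA then subtracts part of that artificial difference from the week 4 comparison, and a change score subtracts all of it. If visit 2 is a time level in the planned repeated-measures ANOVA, the whole shift also enters the time-by-treatment term.

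The trial is a pilot, but the Discussion says that its findings can be used to calculate the effect size for a full-scale trial. A bias of this kind would therefore carry forward.

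**Working it through.** **Step 1. Which visit is the first treatment session?**

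- Number of sessions, from the Bee venom acupuncture section: "BVA intervention will consist of six sessions twice a week for three weeks".
- Timing of the primary endpoint, from Primary outcome measurement: "The primary end point will be the VAS score at the four-week follow-up, one week after the completion of the three-week treatment session". Table 1 places this at visit 8.
- If screening is visit 1, the visits between screening and visit 8 are 2, 3, 4, 5, 6 and 7. That is 6 visits for 6 sessions.
- At two sessions a week, visits 2, 4 and 6 open treatment weeks 1, 2 and 3.

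Visit 2 is therefore most likely both the baseline and the first session. Sessions are booked after allocation, so on the natural reading allocation comes before visit 2, or at the latest on that day. No sentence puts the measures ahead of the envelope.

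**Step 2. Which outcomes have a value from before allocation?**

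| Outcome | Screening | Visit 2 |
|---|---|---|
| VAS bothersomeness (primary) | yes | yes |
| VAS pain intensity | yes | yes |
| NDI, EQ-5D, BDI, SF-36, skin-roll | no | yes |

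**Step 3. How large could the effect be?** The plan gives no figure to reproduce. The following are assumptions that are not in the document: VAS SD 2 cm; correlation r between baseline and week 4 of 0.3 to 0.7, with equal SDs so that the slope equals r; a shift d of 0.25 to 1.0 cm in one arm only; 20 per arm (60/3).

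Bias of the ANCOVA contrast = −r × d. In absolute size:

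- smallest: 0.3 × 0.25 = 0.075 cm, about 0.08
- largest: 0.7 × 1.0 = 0.70 cm

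Standard error of a pairwise difference = SD × √(1 − r²) × √(2/20):

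- r = 0.3: 2 × 0.954 × 0.316 = 0.603 cm
- r = 0.5: 2 × 0.866 × 0.316 = 0.548 cm
- r = 0.7: 2 × 0.714 × 0.316 = 0.452 cm

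The bias is thus between 0.075/0.603 = 0.12 and 0.70/0.452 = 1.5 standard errors. A change score would carry the full 0.25 to 1.0 cm.

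**Step 4. Simulation.** Two arms of 20, no true effect, 4,000 replicates, nominal level 0.05 (two-sided assumed):

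| Covariate and shift | r = 0.3: bias, type I error | r = 0.5: bias, type I error | r = 0.7: bias, type I error |
|---|---|---|---|
| visit 2, d = 0 | −0.01, 0.048 | 0.02, 0.048 | 0.00, 0.049 |
| visit 2, d = 0.25 | −0.07, 0.056 | −0.14, 0.057 | −0.18, 0.070 |
| visit 2, d = 0.5 | −0.14, 0.053 | −0.27, 0.073 | −0.35, 0.110 |
| visit 2, d = 1.0 | −0.30, 0.075 | −0.50, 0.139 | −0.71, 0.310 |
| screening, d = 1.0 | 0.00, 0.053 | 0.00, 0.050 | 0.00, 0.052 |

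The simulation agrees with the formula. It also shows that a covariate recorded before allocation removes the problem for the VAS outcomes. The other outcomes have no such substitute.

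**The case against.** The strongest reply is that the harmful order is inferred. No sentence names the visit at which the envelope is opened or says when the patient learns the arm. The randomization section gives a necessary condition, not a time. Baseline measures, then envelope, then first session, all on the day of visit 2, would not contradict the text. The flowchart is not available here and may show the order. All of this stands, so a reader should not infer that baselines are known to be given after allocation; the text only fails to exclude it.

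Further points that stand:

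- A reader might say that the ANCOVA covariate is contaminated by treatment. The documents do not support that. Scores taken before the first session precede any treatment, and the analysis section does not name the covariate score.
- The primary outcome has a screening value, so it is the less exposed case.
- The shift has no source in the document. All arms receive active treatment and the primary VAS asks about the past week, so the shift may be small. At 0.25 cm the type I error is only 0.056 to 0.070.
- Selective loss between allocation and visit 2 is tempting to add, but the document states no interval between the two.
- The skin-roll test includes caliper thickness, which expectation should not move.
- Hypothesis tests in this pilot are to be treated as preliminary.

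What does not stand is that this is only a detail of condensed reporting. The article does describe the sequence and the condition for allocation, and followed as written they leave the baseline unprotected.

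**Conclusion.** The point holds as a gap in the stated order. Nothing requires the visit 2 measures to be complete before the allocation is revealed, visit 2 is most likely the first session booked after allocation, and patients are open-label. Their self-reported baselines may therefore be affected by knowledge of the arm. The exposure is greatest for NDI, EQ-5D, BDI and SF-36, where visit 2 is the only pre-treatment value.

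For a VAS outcome adjusted for the visit 2 score, the bias would be about 0.08 to 0.7 cm. That range rests wholly on the assumed shift and correlation; the true shift could be zero, and its direction is unknown. It shows how the mechanism scales and does not estimate what will happen. The correction is nearly free and worth making.

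**What to change.** 1. In the randomization section, state that the envelope is opened only after the visit 2 baseline measures (both VAS scales, NDI, EQ-5D, BDI, SF-36 and skin-roll) are recorded.
2. In the analysis section, name the screening VAS as the ANCOVA covariate for bothersomeness and for pain intensity, for all patients alike. A rule that varies by patient would mix covariates of different reliability in one model.
3. Recruitment began in July 2013, so some patients may already have been allocated before visit 2. For them, report the other baseline-adjusted outcomes with that caveat.

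Cost: one sentence in each of two sections and a changed order of steps at an existing visit, with no added visits, staff or patients. Sessions can be booked only once the visit 2 measures are done. The trial is well under way (completion is expected by July 2014), so the reordering may reach few patients, whereas the covariate choice applies to all. The screening VAS may correlate slightly less with week 4 than the visit 2 score. Even a fall from 0.5 to 0.3 would raise the standard error only from 0.548 to 0.603 cm (0.603/0.548 = 1.10, about 10%).

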### Eligibility criteria

Patients between 18 and 65 years of age who can read and write in Korean, who agree to participate after providing written informed consent, and who have been experiencing non-specific, uncomplicated neck pain for at least three months preceding the time of the screening visit will be selected as study volunteers.

Patients will be excluded from the study if they have: 1) exhibited abnormalities on neurological examination (such as cervical nerve function, deep tendon reflexes, voluntary muscle activation and sensory function); 2) radicular pain; 3) serious spinal disorders including malignancy, vertebral fracture, spinal infection or inflammatory spondylitis; 4) other chronic diseases that could affect or interfere with the therapeutic outcomes including cardiovascular disease, diabetic neuropathy, active hepatitis, fibromyalgia, rheumatoid arthritis, dementia or epilepsy; 5) previous spinal surgery or scheduled procedures during the study; 6) a painful condition induced by a traffic accident; 7) a substantial musculoskeletal problem generating pain from an area other than the neck; 8) conditions for which administration of BVA might not be safe including clotting disorders, administration of an anticoagulant agent, pregnancy and seizure disorders; 9) a documented hypersensitive reaction to previous BVA treatments, bee stings or insect bites; 10) a positive reaction observed during a skin hypersensitivity test; 11) a severe psychiatric or psychological disorder; 12) current use of corticosteroids, narcotics, muscle relaxants or herbal medicines to treat neck pain or any medication considered inappropriate by the investigator; and 13) pending lawsuits or receipt of compensation due to neck pain.

